### Participants

#### Sample size calculation

Since there were no available MS CBT trials using either of our primary outcomes we computed a power analysis calculation based on a recent CBT trial for depression in people with MS, which used the Beck Depression Inventory (BDI) as the primary outcome [28]. The BDI, like the GHQ (one of our primary outcomes) is a measure of affective distress. Using a conservative estimate for the within-group standard deviation the effect size from this study was .60. To achieve 80% power at alpha = 0.025 significance level (to adjust for two primary outcomes) we would need 55 patients in each group to detect an effect of this magnitude by an independent samples t-test. To allow for attrition of around 10% at follow-up we need to initially include 61 participants in each group. In our CBT for MS fatigue trial we only lost 3/72 patients to follow-up (4%).

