### Primary outcome measures

There are two primary outcomes.

1. The General Health Questionnaire (GHQ) [41] is designed to measure general levels of distress in people in the community and medical settings. The measure is uncontaminated by the experience of MS related somatic symptoms and a recent study showed the GHQ was the most treatment responsive measure of psychological distress in three discrete MS samples [42].

2. The Work and Social Adjustment Scale (WSAS) [43] is a self-report scale of functional impairment attributable to an identified illness, in this case MS. The scale measures how much MS interferes with a person's work, home management, social leisure activities, private leisure activities, and the ability to form and maintain close relationships.

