#### Statistical analysis plan

Statistical analysis will be carried out in SPSS and/or Stata general purpose statistical analysis packages. Mediation modeling may require use of specialist structural equation modeling software (e.g. AMOS or M-Plus).

All treatment group comparisons will be carried out on an intention-to-treat basis, that is subjects will be analyzed in the group to which they were randomized irrespectively of the treatment received. The primary and secondary longitudinal outcomes will be analyzed using linear mixed modeling. In these models the outcome variable at the post-treatment time points will be the dependent variable and baseline values of the outcome variable, centre, time (post-treatment, 6 M follow-up or 12 M follow-up), group (CBT or Supportive Listening) and a time × group interaction terms will feature as explanatory variables. To account for correlation between measures taken on the same individual at various time points subject-varying random intercepts and slopes of time will also be included in the model. Further baseline variables might be used as explanatory variables, to provide more powerful group comparisons if they are found to be predictive of the outcome variable. As the model fitting will by maximum likelihood such analyses are valid if missing data arises at random (MAR). The effect of informative missingness processes will be explored by means of a formal sensitivity analysis [54].

We will further investigate whether results were unduly influenced by patients who have shown marked disease progression during the trial or who have altered medication during the trial period. We will also assess the sensitivity of the results to excluding patients who did not receive a sufficient number of treatment sessions or those who had low expectations of the therapy they received.

An approach similar to Baron and Kenny's mediation modeling [55]will be used to explore whether change of psychological outcomes mediates the path from therapy to change in MS adjustment. Specifically we will use instrumental variable methods advocated by Dunn and colleagues to try and adjust for unobserved confounders of the path from mediations to outcomes [56,57].

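### Fitting the primary mixed models by maximum likelihood makes standard errors about 1.5–2% too small, so each primary test runs at about 0.027–0.028 instead of 0.025 (minor)

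*Protocol article*

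**What the plan says.** The Statistical analysis plan section analyses the primary and secondary longitudinal outcomes with linear mixed models. The fixed effects are the baseline value of the outcome, centre, time (three post-treatment assessments), group, and group by time. Subjects have random intercepts and random slopes of time. The estimation method is named in the sentence on missing data: "As the model fitting will by maximum likelihood such analyses are valid if missing data arises at random (MAR"). The section does not mention restricted maximum likelihood (REML), degrees of freedom or a reference distribution.

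The Primary outcome measures section states "There are two primary outcomes", and the Abstract places them at twelve months. The Sample size calculation section sets the level for each: "To achieve 80% power at alpha = 0.025 significance level (to adjust for two primary outcomes"). It expects 55 evaluable patients per group.

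**The concern.** Maximum likelihood estimates the variance components as if the fixed effects were known. In a large trial the difference is negligible. With about 110 subjects, and a contrast that depends mainly on between-subject variation, it is small but visible: variances, and therefore standard errors, are biased downward.

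The direction matters because the design splits alpha between GHQ and WSAS to hold 5% overall. An estimator that understates standard errors gives part of that protection back, and it favours declaring a difference between CBT and Supportive Listening. The reason given for maximum likelihood, validity under MAR, does not require it, because REML is also likelihood-based and shares that property.

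**Working it through.** **Inputs**
- From Sample size calculation: alpha 0.025 per outcome, 80% power, effect size 0.60, 55 evaluable per group (N = 110), 61 per group randomised (122 in total).
- From Statistical analysis plan: maximum likelihood and the fixed effects listed there.
- Assumed: a two-sided test (sidedness is not stated), and p = 4 coefficients acting on the group comparison at a given visit (intercept, baseline, centre, group).

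**The plan's own figure.** A noncentral t calculation at two-sided alpha 0.025 and d = 0.60 gives power 0.799 at 54 per group and 0.807 at 55. So 55 is reproduced. With one-sided 0.025 the normal approximation gives only 44, so two-sided is meant. For attrition, 55/0.9 = 61.1, in line with the stated 61.

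**Standard error under maximum likelihood.** The ratio to the unbiased standard error is √((N − p)/N) = √(106/110) = 0.982, or 1.8% too small.

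**Actual size of each test.** The size is P(|t| > c × 0.982) on 106 degrees of freedom, where c is the critical value used.
- t reference: c = 2.274; 2.274 × 0.982 = 2.232; size 0.0277.
- Normal reference: c = 2.241; 2.241 × 0.982 = 2.200; size 0.0300.
- Normal reference with REML, for comparison: P(|t| > 2.241) = 0.0271.

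**Sensitivity**

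| N | p | t reference | Normal reference |
|---|---|---|---|
| 110 | 4 | 0.0277 | 0.0300 |
| 110 | 5 | 0.0285 | 0.0308 |
| 110 | 6 | 0.0292 | 0.0316 |
| 122 | 4 | 0.0275 | 0.0294 |

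The rows with p = 5 and 6 are relevant because the plan allows further baseline covariates.

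**Simulation of the planned model under the null.** The model had three visits, random intercept and slope, baseline, centre, and group by time, and the test was of the group difference at 12 months. N = 110, complete data, 35,200 replicates, Monte Carlo standard error 0.0008. The variance components are assumed, since the article gives none. The median ratio of ML to REML standard errors was 0.985, about 1.5% too small.

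| Fit | t reference (106 df) | Normal reference |
|---|---|---|
| ML | 0.0274 | 0.0295 |
| REML | 0.0249 | 0.0274 |

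**Interval width.** With a t reference, ML intervals are 0.982 of the correct width (1.8% narrow). With a normal reference the factor is 0.982 × (2.241/2.274) = 0.982 × 0.986 = 0.968 (3.2% narrow).

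**Both outcomes together.** If GHQ and WSAS were independent:
- planned: 1 − 0.975² = 4.9%
- ML with t: 1 − (1 − 0.0277)² = 5.5%
- ML with normal: 1 − (1 − 0.0300)² = 5.9%

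Their correlation is not given. Treating the two test statistics as bivariate normal, ML with t (0.0277 each) gives 5.1% at r = 0.5 and just under 5% at r = 0.6.

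**The case against.** The sentence quoted is there to justify validity under MAR, and as a statement about MAR it is correct. It does not weigh ML against REML, and a reader could take maximum likelihood as loose shorthand covering both. Degrees of freedom and reference distribution are details that an article normally leaves to the full analysis plan, which is not shown. The excess is about a quarter of a percentage point per test.

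Much of this stands. The MAR statement is not an error, the silence on degrees of freedom is not a fault of the article, and the inflation arises only if full ML is used as written. What remains is that the article names an estimator, and the one it names works against its own alpha split.

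Three stronger readings are not supported.
- A reader might infer that each test runs at 0.030 with intervals 3% too narrow. That also needs a normal reference, which the article nowhere states and which by itself gives about 0.027 even under REML.
- A reader might infer that the 5% family-wise limit is necessarily broken. The 5.5–5.9% range assumes independent outcomes, whereas both are adjustment measures taken on the same patients.
- A reader might fault the choice of "SPSS and/or Stata general purpose statistical analysis packages". That is unspecified detail, neither wrong nor contradictory.

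**Conclusion.** The point holds as a minor one. Fitted by full maximum likelihood as written, with about 110 evaluable participants, the primary tests run at about 0.027–0.028 each with a t reference. The upper figure of about 0.030 is conditional on a normal reference. The loss of family-wise protection ranges from about half a percentage point with a t reference and independent outcomes to nothing once the correlation reaches about 0.6.

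These figures rest on two-sided testing, about four between-subject coefficients and, in the simulation, assumed variance components and complete data. The sample size is unaffected, because it was derived from a t-test. A conclusion would change only for a p-value close to 0.025.

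**What to change.** State that the GHQ and WSAS models, and the secondary ones, are fitted by restricted maximum likelihood, and that the 12-month group contrast is tested with a t reference using Kenward–Roger or Satterthwaite degrees of freedom. The MAR justification can stay, since it applies equally to REML. In the simulation, REML with a t reference on 106 degrees of freedom returned the size to 0.0249.

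The cost is one sentence of wording. Intervals become wider by 1/0.982, about 2%, compared with ML and a t reference, or by 1/0.968, about 3%, compared with ML and a normal reference. No extra patients or data are needed.

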### Economic evaluation plan

Service use measured with the CSRI will be combined with relevant unit costs (e.g. [58]). The cost of the interventions will be calculated using information on therapist pay as well as training and supervision costs and overheads. Cost comparisons will be made between the two groups using bootstrapping methods to account for non normality in the data distribution.

Service cost data will be combined with the primary outcome measures (GHQ and WSAS) and quality-adjusted life years (QALYs), generated from the EQ-5D to assess cost-effectiveness. If the intervention has lower costs and better outcomes then it will be 'dominant'. In the event of the intervention having higher service costs and better outcomes, cost-effectiveness will be assessed using incremental cost-effectiveness ratios. To address uncertainty in cost and outcome differences we will use cost-effectiveness planes (CEPs) which will show the probability of the intervention being (i) cost-saving and more effective, (ii) cost-saving and less effective, (iii) cost-increasing and more effective and (iv) cost-increasing and less effective. Cost-effectiveness acceptability curves (CEACs) will be generated to show the probability that the intervention is cost-effective for different values placed on a unit improvement in the GHQ/WSAS or one extra QALY gained. CEPs will involve producing a large number of cost-outcome combinations using bootstrap methods and plotting these on a plane where one axis represents incremental costs and the other incremental outcome. CEACs will be generated by computing 'net benefits' for each participant (defined as the monetised value of outcome minus service costs). The value of a unit improvement in outcome is unknown and therefore a range of values will be used resulting in a number of different net benefits for each participant. Regression analyses will be used to estimate the difference in net benefits between the two arms for each value placed on a unit improvement in outcome. Bootstrapped regression coefficients of these differences will be saved and the proportion that are above zero will indicate the probability that one arm is more cost-effective than the other.

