#### Secondary Aims

2) To examine whether the CBT and SL groups differ on a range of secondary outcomes including quality of life, acceptance of illness and dysfunctional cognitions.

3) To examine whether changes in predefined psychological mechanisms act as mediators through which change/adjustment in our primary outcomes occurs. These proposed mediating factors are dysfunctional or unhelpful cognitions and behaviours, and acceptance of illness.

4) To examine whether patients' responses to treatment is moderated by therapeutic alliance factors, patients' treatment preference, engagement in homework tasks, and perceived social support.

5) To examine the cost-effectiveness of both interventions by taking into account benefits to patients, effects on health service usage and other costs to society, and cost of providing the interventions.

6) To evaluate both interventions from the perspective of the person with MS using in-depth interviews and qualitative analysis methods to elicit their experiences of the therapy, any changes it brought, and any helpful and unhelpful aspects.

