### Service use and QALYs

Service use (additional to the CBT intervention or Supportive Listening which will both be centrally recorded) by patients in both arms of the trial will be measured using the Client Service Receipt Inventory (CSRI) [51]. This will record health and social service contacts in the six months prior to baseline assessment, and the periods prior to 6- and 12-month follow-up interviews. Time lost from work because of MS-related problems will also be measured.

The EuroQol (EQ-5D) [44], a 5 item composite measure which considers mobility, self-care, usual activities, pain/discomfort and anxiety/depression will be used to assess quality of life. The EQ-5D will be used to generate quality adjusted Life Years (QALYs) [52].

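### Cost-effectiveness is defined on service costs only, so the lost work time that is measured never enters the result and the costs-to-society part of Aim 5 goes unanswered

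*Protocol article*

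**What the plan says.** Four places in the protocol article bear on this.

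- **Secondary Aims, item 5.** Cost-effectiveness is to take account of patient benefit and of "effects on health service usage and other costs to society, and cost of providing the interventions".
- **Service use and QALYs.** The Client Service Receipt Inventory (CSRI) supplies service use: "This will record health and social service contacts in the six months prior to baseline assessment", and again for the periods before the 6- and 12-month follow-ups. Then: "Time lost from work because of MS-related problems will also be measured". EQ-5D supplies the QALYs. Table 1 schedules both CSRI and EQ-5D at baseline, week 26 and week 52.
- **Economic evaluation plan, building the costs.** "Service use measured with the CSRI will be combined with relevant unit costs". "The cost of the interventions will be calculated using information on therapist pay as well as training and supervision costs and overheads". No other cost is constructed.
- **Economic evaluation plan, using the costs.** "Cost comparisons will be made between the two groups using bootstrapping methods". Service cost data are then set against GHQ, WSAS and QALYs. ICERs apply when service costs are higher and outcomes better. Net benefit, which drives the acceptability curves, is the "monetised value of outcome minus service costs". For those curves, "Regression analyses will be used to estimate the difference in net benefits between the two arms"; covariates are not mentioned.

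**The concern.** The aim promises a cost base wider than services, and the trial collects the main item needed for it. The analysis section does not leave the cost definition open: it gives one, and that definition is narrower than the aim. If the section is followed as written, the lost-work data have no stated use.

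This matters because incremental intervention cost may be small. Both arms receive eight sessions on the same timetable, from the same nurse in each centre, so therapist time should be close to equal. What remains is mainly training (Table 2 gives 32.5 hours for CBT and 13 for Supportive Listening) and supervision. The trial also aims to improve role functioning, and one primary outcome, WSAS, asks about interference with work. Lost work is therefore a plausible place for the arms to differ in cost. It could affect whether CBT is called dominant or is assessed by an ICER. If the perspective is settled only after the results are known, the choice is open to the charge that it followed them.

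**Working it through.** **1. Perspective: the text side by side.**

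| Element of Aim 5 | Data collected | Enters the cost-effectiveness result? |
|---|---|---|
| Patient benefit | GHQ, WSAS, EQ-5D | Yes |
| Health service use | CSRI | Yes, with unit costs |
| Cost of the interventions | Central records; pay, training, supervision, overheads | Costed; read here as part of service cost |
| Other societal costs | Time lost from work | No valuation and no use stated |

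**2. What the omission does to net benefit.** For participant i, let E be outcome, λ the value of one unit of outcome, C service cost, L days of work lost and w the value of a day.

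- As written: NB = λE − C.
- With lost work: NB* = λE − C − wL.
- Between arms (CBT minus Supportive Listening): ΔNB* = ΔNB − wΔL, and incremental cost becomes ΔC + wΔL.

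The shift wΔL is the same at every λ, so it moves the whole acceptability curve. It reverses the sign of incremental cost when it is opposite in sign to ΔC and larger in size. The documents give neither w nor ΔL. Purely as an assumption, 2 days × £100 = £200 and 10 days × £100 = £1,000 per patient, in either direction.

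**3. Group size, needed for step 4.** The economic plan has no figure of its own. The sample size section states effect size 0.60, alpha 0.025, 80% power, 55 per group and 61 after 10% attrition. A two-sided t-test (sidedness is assumed) needs 54.08, rounded up to 55; power at 55 is 80.7%; and 55/0.9 = 61.1. The stated figures reproduce and are not at issue.

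**4. What baseline adjustment would gain.** Assumptions, none of them in the documents: QALYs by the trapezium rule, EQ-5D SD 0.20 to 0.30, and baseline-to-follow-up slope ρ from 0 to 0.7.

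- QALY = 0.25·u0 + 0.5·u26 + 0.25·u52.
- SE of the chance baseline difference = SD × √(2/55): 0.20 gives 0.038 and 0.30 gives 0.057.
- Unadjusted carry-over per one SE of imbalance = SE × (0.25 + 0.75ρ). Lowest: 0.0381 × 0.25 = 0.0095 QALY. Highest: 0.0572 × 0.775 = 0.044 QALY.
- Variance of a single follow-up measure left after adjustment = 1 − ρ²: 0.91, 0.75 and 0.51 for ρ = 0.3, 0.5 and 0.7.

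**The case against.** The best case for the plan has several parts.

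- **Most of Aim 5 is covered.** A reader might infer that the plan cannot answer Aim 5 at all. The documents do not support that: patient benefit, service use and intervention cost are all provided for, and the CSRI reaches beyond health services to social services. One could even read the societal wording as meaning social services. Under that reading, however, lost work would be measured for no stated analysis, so a clarifying sentence is still needed.
- **Not every cost term is limited to services.** The cost-comparison sentence, the dominance rule and the axis of the cost-effectiveness plane speak of costs without qualification, so it would be wrong to say that every economic quantity is expressly service-only. This stands. But no cost of lost work is built anywhere, and the three definitions that are explicit (the cost-outcome combination, the ICER condition and net benefit) all say service costs.
- **This is a journal article, with a separate economic paper planned.** Detail can be left to a fuller plan. That answers a gap but not a stated definition that conflicts with a stated aim.
- **Baseline adjustment.** A reader might infer that the arms will be compared without baseline costs and utilities, and that the result will be biased. The article says neither. It plans a regression for net benefit and is silent on covariates, which an article may leave to the full plan. It names baseline value and centre as covariates in its models for the longitudinal clinical outcomes. Patient-level randomisation, stratified by centre, keeps an unadjusted contrast unbiased in expectation. This objection stands in full.

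**Conclusion.** The perspective point holds on the text alone. Aim 5 includes societal costs, lost work is measured, and the cost-effectiveness result is defined without it, so that one part of one secondary aim is not answered. No conclusion on the primary outcomes depends on it.

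Its numerical size cannot be derived from the documents; the £200 to £1,000 per patient follows wholly from an assumed difference in days and an assumed day rate. That lost work could change the sign of incremental cost is a possibility, not something the documents show.

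Baseline adjustment is a recommendation for precision and for protection against chance imbalance, not the correction of an error. The range of about 0.01 to 0.04 QALY per standard error of imbalance rests on the assumed SD, slope and QALY method.

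**What to change.** In the Economic evaluation plan, before the treatment codes are broken, do one of the following.

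- **Add a second perspective.** Run the ICER, the cost-effectiveness plane and the acceptability curve (a) on service plus intervention costs and (b) on those costs plus valued lost work time. State the wage or unit-value source. For (b), use QALY and GHQ as outcomes; WSAS already scores work, so pairing it with a cost for lost work would count the same loss twice.
- **Or narrow Aim 5** to a health and social service perspective, and say what the lost-work data are for.

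In either case, consider including baseline CSRI cost, the baseline value of the outcome concerned (EQ-5D utility, GHQ or WSAS) and centre in the cost, QALY and net-benefit regressions, and bootstrapping those adjusted models.

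The first option costs one extra analysis run and a valuation source, which the article does not name. Narrowing the aim costs a sentence. The covariates are already in the assessment schedule or, for centre, in the randomisation record.

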#### Qualitative analysis plan

A thematic analysis of the participants' therapy experience interviews will be conducted based upon procedures described by Boyatzis and Joffe and Yardley [59,60]. This will involve an inductive approach whereby transcripts are coded in order to develop conceptual categories which describe salient themes in the data. Elements of grounded theory practice [61,62] will also be incorporated; constant comparison, "in vivo" coding, attention to discrepant cases and memoing. Once all transcripts are coded and a comprehensive coding manual has been developed and refined we will inspect the data for patterns and relationships in the themes within and between the two therapy groups.

